## 11. Efficacy assessment criteria, assessment method, and analysis method (Data analysis method)

### 11.1 Assessment criteria

Primary and secondary validity assessment variable is as follows and each assessment variables are analyzed with classification of futhan and no-anticoagulation group.

#### 11.1.1 Primary validity assessment variable

Mortality at ICU

#### 11.1.2 Secondary validity assessment variables

- ① Mortality in hospital
- ② Mortality at 28 days after initiation of CRRT
- ③ CRRT duration
- ④ Hospitalization period in ICU
- ⑤ Hospitalization period
- ⑥ .Survival period
- ⑦ Filter life span
- ⑧ Blood loss
- ⑨ Transfusion

### 11.2 Assessment method

#### 11.2.1 Primary validity assessment variable

Mortality at ICU:

We will check whether patients' mortality at ICU after CRRT is 50% and additionally whether there is any statistically significant difference between two groups.

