#### 3.1 Purpose

##### 3.1.1 Primary end point

We are planning to compare mortality in ICU between nafamostat mesilate group and no-anticoagulation group in patients who are not fit to use heparin due to hemorrhagic tendency.

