### 6.3.2 Estimation basis

Primary end point of this clinical study is to evaluate the mortality of Futhan group and compare it to mortality of no-anticoagulation group.

Generally, the mortality of CRRT patients in ICU is known to be roughly 50% [1,4,5].

Thus, we anticipate the mortality in futhan group as 50% and assume the tolerance as 15% to estimate actual mortality. Also, we will add the same number of no-anticoagulation subjects to compare with futhan group on mortality.

Level of significance, ( $\alpha = 0.1$ )

Allowable limits of error for mortality are 15%. ( $\delta=0.15$ )

Considering the patient's severity in ICU, wastage rate is set at 5%. ( $r = 0.05$ )

Hence, necessary number of subjects is calculated after the following formula;

$$n_t = \frac{Z_{1-\alpha/2}^2 p(1-p)}{\delta^2}$$

By this formula, we estimate necessary number of subjects and calculate the final number of subjects by considering drop-out rate using the following formula.

$$n = \frac{n_t}{1-r}$$

The necessary number of subjects is 31 patients per group, and considering the 5% drop out rate, the final number would be 33 patients per group.

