### 11.3.3 Validity data

#### 11.3.3.1 Primary validity assessment value

Mortality at ICU is presented.

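### Section 11.2.1 leads the primary assessment with a check of ICU mortality against 50% and puts the randomised comparison second, contrary to the purpose in section 3.1.1

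*Protocol*

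**What the plan says.** Section 3.1.1 gives the primary purpose as a comparison of randomised groups: "We are planning to compare mortality in ICU between nafamostat mesilate group and no-anticoagulation group". Sections 3 and 7.1 describe a randomised open study whose aim is to compare mortality, among other outcomes, between nafamostat and no anticoagulation.

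Section 11.2.1, which sets out how the primary variable is assessed, says the investigators will check whether "mortality at ICU after CRRT is 50% and additionally whether there is any statistically significant difference between two groups". It does not say whether the check applies to the futhan group, to each group or to all patients, or what would count as agreement with 50%. Section 11.2.2 (1) and (2) use the same construction for in-hospital mortality and for mortality 28 days after CRRT initiation.

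The 50% comes from section 6.3.2: "Generally, the mortality of CRRT patients in ICU is known to be roughly 50" per cent, with literature references. The same section opens with a two-part statement, "Primary end point of this clinical study is to evaluate the mortality of Futhan group and compare it to mortality of no-anticoagulation group", and then sizes the study for the first part: "we anticipate the mortality in futhan group as 50% and assume the tolerance as 15% to estimate actual mortality". The control group is added at the same number.

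**The concern.** A reader of section 3.1.1 expects the primary result to be a difference between two concurrent randomised groups. A reader of section 11.2.1 expects first a statement on whether mortality matches a published figure, and then, as an extra, whether the groups differ. These are different questions and can have different answers.

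The check against 50% does not use the randomisation. Its reference is a rough figure for CRRT patients in ICU generally. Section 6.1 enrols a narrower population: hemodynamically unstable patients with at least one hemorrhagic criterion, among them septic shock or DIC. Case mix alone can move observed mortality away from 50% in either direction, in both groups alike. Nor is it clear what the check would conclude: failure to reject 50% does not establish that mortality is 50%.

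At stake is which result counts as the trial's primary answer. An analysis plan that follows section 11.2.1 as written would lead with a finding that does not address the stated purpose.

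**Working it through.** **1. The plan's own figure.** Inputs from section 6.3.2: p = 0.50, tolerance 0.15, alpha = 0.10 with Z at 1 − alpha/2 = 1.645, drop-out 5%.

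- n = 1.645² × 0.5 × 0.5 / 0.15² = 30.06, rounded up to 31.
- 31 / (1 − 0.05) = 32.6, rounded up to 33.

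The stated 31 and 33 per group reproduce. The formula is for the precision of a single proportion. It contains no between-group difference and no power.

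**2. What the check against 50% can tell.** Section 11.2.1 gives no test, alpha or group for the check, so these figures are illustrations. I assume an exact two-sided binomial test of 0.5 at the sizing alpha of 0.10.

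| Patients | 50% retained for | Rejected if true mortality is 35% | Rejected if true mortality is 40% |
|---|---|---|---|
| 31 (one group) | 11 to 20 deaths (35.5% to 64.5%) | 45.5% | 24.7% |
| 62 (both pooled) | 25 to 37 deaths (40.3% to 59.7%) | 77.4% | 47.3% |

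The pooled row takes the same true mortality in both groups. Now set the check beside an assumed drug effect:

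- Both groups at 35%, no drug effect: 50% is rejected in 46% of trials with 31 patients and in 77% with 62 pooled.
- Groups at 65% and 35%, a 30-point difference, pooled: the expected rate is (65 + 35)/2 = 50%, and 50% is rejected in about 8% of trials.
- Futhan group at 50% and checked alone: 50% is rejected in about 7% of trials whatever the control group's mortality, so the result is the same for any size of drug effect.

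The check can therefore signal when the drug does nothing and stay silent when it does a great deal. The cause is the question asked, so a larger sample would not cure it.

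**3. What the randomised comparison can do at this size.** Two-sided test of two proportions with pooled variance under the null, 31 per group, alpha 0.10. The difference of 50% versus 35% is an assumption: it borrows the protocol's 15 points, which section 6.3.2 uses as a tolerance and not as a treatment effect.

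- Pooled rate (0.50 + 0.35)/2 = 0.425; standard error under the null √(2 × 0.425 × 0.575 / 31) = 0.1256.
- Standard error under the alternative √((0.50 × 0.50 + 0.35 × 0.65)/31) = 0.1241.
- Power = Φ((0.15 − 1.645 × 0.1256)/0.1241) = Φ(−0.46) ≈ 32%.

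On the same basis, power is 49% for 50% versus 30% and 81% for 50% versus 20%.

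**The case against.** The strongest reply is that the between-group test is promised in the same sentence as the check. Sections 3, 3.1.1, 6.3.2 and 7.1 all state the comparison as an aim, and section 11.1 says each variable is analysed by group. On that view only the order of two planned analyses is at issue, and it hangs on one adverb. This stands in part. A reader might infer that the trial answers its primary question only against an external constant and so cannot show a drug effect. The documents do not support that: the comparison is committed to, and the limitation belongs to the one-sample check alone.

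A second reply is that section 6.3.2 treats the 50% in terms of estimation and that no hypothesis test of it is stated; the intention may be no more than to set observed mortality beside the expected rate. This also stands, and the rejection rates above are therefore illustrative. It would be wrong, too, to say that a sample of 31 almost guarantees retaining 50%: under the assumed test, 50% is rejected in 45.5% of trials at a true 35%. But if description is all that is meant, section 11.2.1 should not make it the lead primary assessment.

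Section 11.3.3.1 says only "Mortality at ICU is presented". A reader might take that as a further fault. The choice of test and interval is detail commonly left to an analysis plan, and none is shown here, so I do not count it.

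The order is unlikely to be a slip. It recurs in section 11.2.2 for two more mortality endpoints, and the sample size follows the same one-sample logic.

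**Conclusion.** The point holds in a limited form. Sections 3.1.1 and 11.2.1 disagree on the primary question: the first names the randomised comparison, the second leads with a check against 50% in an unnamed group. That check cannot separate a drug effect from case mix, and its result is not an answer to the trial's stated purpose. The comparison that does answer it is planned, but in second place.

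The contradiction and the unnamed group rest on the text alone. The size of the problem (50% retained for 11 to 20 deaths of 31; rejection in 46% or 77% of trials with no drug effect) rests on an assumed exact two-sided test at alpha 0.10 and on assumed mortality rates. The correction matters because it settles which result is primary. Making it also exposes that 31 per group was never sized for the comparison.

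**What to change.** - **Section 11.2.1:** state that the primary analysis is the difference in ICU mortality between the randomised groups, nafamostat minus no anticoagulation, with its confidence interval. Report each group's mortality with an interval as description only, and remove the check against 50%. The choice of test can stay with the analysis plan.
- **Section 11.2.2 (1) and (2):** make the matching change for in-hospital and 28-day mortality.
- **Section 6.3.2:** say plainly that 31 per group was set by one-sample precision, and give the power of the between-group comparison at that size: about 32% for 50% versus 35% at two-sided alpha 0.10, with the difference labelled as an assumption.

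The cost is a few sentences in sections 11 and 6 and no new data. The rewording does not raise the power. If the sponsor wants the comparison to be adequately powered, the sample size has to be reconsidered, and that is a larger decision than this correction.

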#### 11.2.2 Secondary validity assessment variables

(1) Mortality in hospital

We will check whether the patients' mortality in hospital after CRRT is 50%, and additionally whether there is any statistical significant difference between two groups.

(2) Mortality at 28 days after initiation of CRRT

We will check whether the patients' mortality at 28 days after initiation of CRRT is 50%, and additionally whether there is any statistical significant difference between two groups.

(3) CRRT duration

We will check the duration of CRRT at ICU between the two groups.

(4) Hospitalization period in ICU

We will check the patients' duration within ICU until recovery to general ward or death.

(5) Hospitalization period

We will check the patients' duration within hospital until discharge or death.

(6) Survival period

We will calculate the survival 28 days after CRRT in both groups. Each patient's survival period is sought to calculate median survival time.

(7) Filter life span

We will check each filter life span during CRRT when CRRT is discontinued and calculate average filter life span.

(8) Blood loss

We will check blood loss at filter change during CRRT.

(9) Transfusion

We will check the amount of transfusion during CRRT.

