#### 11.3.3.2 Secondary validity assessment value

(1) Mortality within hospital

Mortality within hospital is presented.

(2) Mortality at 28 days after initiation of CRRT

Mortality at 28 days after initiation of CRRT is presented.

(3) CRRT duration

The mean, standard deviation, maximum, minimum values of CRRT duration in each group are presented.

(4) ICU hospitalization period

The mean, standard deviation, maximum, minimum values of ICU hospitalization period after ICU initiation in each group are presented.

(5) Hospitalization period

The mean, standard deviation, maximum, minimum values of hospitalization period after CRRT initiation in each group are presented.

(6) Survival

Survival rate at 28 days after initiation of CRRT is calculated using Kaplan-Meier analysis with data of all subjects in the clinical study including censored data. Also, Kaplan-Meier curve is presented as graph, and median survival time of each group is presented.

(7) Filter life span

The mean, standard deviation, maximum, minimum values of filter life span which is changed during the study in each patient are presented.

(8) Blood loss

The mean, standard deviation, maximum, minimum blood loss during each filter change in CRRT with each patient are presented.

(9) Transfusion

The mean, standard deviation, maximum, minimum values of transfusion during CRRT in each patient are presented.

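### ICU and hospital stay end at recovery or at death and are averaged together, so a shorter group mean cannot be read as better or worse

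*Protocol*

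**What the plan says.** Section 11.1.2 lists CRRT duration, ICU stay and hospital stay among the nine secondary validity (efficacy) variables. The synopsis and section 3.1.2 present them as comparisons between the two groups.

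- **ICU stay**, 11.2.2 (4): "duration within ICU until recovery to general ward or death".
- **Hospital stay**, 11.2.2 (5): "duration within hospital until discharge or death".
- **CRRT duration**, 11.2.2 (3): no end event is given.

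Section 11.3.3.2 (3)-(5) summarises all three in the same form. For CRRT it reads "The mean, standard deviation, maximum, minimum values of CRRT duration in each group are presented". Nothing in 11.3.3.2 separates survivors from deaths for these variables, treats death as a competing event or gives deaths a worst value. Kaplan-Meier analysis is planned only for 28-day survival.

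On expected mortality, section 6.3.2 states "Generally, the mortality of CRRT patients in ICU is known to be roughly 50" per cent.

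**The concern.** For ICU and hospital stay, one number stands for two opposite outcomes. Five days in ICU may be a patient who left for the ward on day 5 or one who died on day 5. If about half the patients die in ICU, roughly half the ICU stays end in death, and death in ICU is the primary endpoint. A difference in mean stay therefore mixes speed of recovery with the frequency and timing of death, and the planned summary cannot separate them.

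At stake is the reading of two secondary efficacy comparisons, and probably a third. A group whose patients die earlier can appear to recover faster, and a treatment that delays or prevents death can appear to prolong the stay. The primary endpoint is not affected.

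**Working it through.** **The plan's own figure.** The protocol gives no figure for the durations. Its group size supplies the number of patients per mean. Section 6.3.2 uses p = 0.5, α = 0.10 (two-sided) and δ = 0.15:

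n = 1.645² × 0.5 × 0.5 / 0.15² = 30.06, rounded up to 31. Then 31 / 0.95 = 32.6, rounded up to 33.

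This agrees with "The necessary number of subjects is 31 patients per group" and with 33 enrolled per group.

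**Inputs for the check**

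- m, mortality: 50% from section 6.3.2; other values are what-if cases.
- S, mean stay of survivors, and D, mean time to death: not in the protocol, so assumed and varied.
- S is the same in both groups throughout, so true speed of recovery never differs.

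**Formula.** Pooled mean stay = m × D + (1 − m) × S. A change in mortality of Δm shifts the mean by Δm × (D − S). At fixed m, a change in time to death of ΔD shifts it by m × ΔD.

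**More deaths, D = 8 and S = 20**

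- 40%: 0.4 × 8 + 0.6 × 20 = 15.2 days
- 50%: 0.5 × 8 + 0.5 × 20 = 14.0 days
- 60%: 0.6 × 8 + 0.4 × 20 = 12.8 days

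**More deaths, 65% against 50%, other assumptions**

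| S (days) | D (days) | Mean at 50% | Mean at 65% | Shift |
|---|---|---|---|---|
| 10 | 7 | 8.50 | 8.05 | −0.45 |
| 14 | 5 | 9.50 | 8.15 | −1.35 |
| 20 | 3 | 11.50 | 8.95 | −2.55 |
| 14 | 14 | 14.00 | 14.00 | 0.00 |
| 14 | 20 | 17.00 | 17.90 | +0.90 |

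The sign depends on whether D is below or above S.

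**Earlier deaths, 50% mortality in both groups, S = 14.** Deaths at day 7 on average: 0.5 × 7 + 0.5 × 14 = 10.5 days. Deaths at day 3: 0.5 × 3 + 0.5 × 14 = 8.5 days. The shift is −2.0 days. Because m × ΔD does not involve S, this direction holds whatever the survivors' stay.

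**Chance of a misleading ranking.** Trials with 31 per group were simulated (20,000 per case, lognormal stays, assumed coefficient of variation 0.7, S = 14). The group with worse survival had the shorter mean stay in:

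- 75% of trials for 65% against 50% mortality (D = 5);
- 90% for 65% against 35% (D = 5);
- 82% for equal mortality with deaths at day 3 against day 7.

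**Same cases with event-free days to day 28, death scored 0.** With S = 14 and no spread, a survivor scores 28 − 14 = 14. The mean is 0.5 × 14 = 7.0 days at 50% mortality and 0.35 × 14 = 4.9 at 65%, so the group with more deaths scores worse. In the simulation that group scored lower in 85% of trials (65% against 50%). When only the timing of death differed, the ranking was even (50%).

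**CRRT duration.** Section 8.2.5 foresees deaths during CRRT, and footnote 2 of the schedule in 8.1 uses the last examination before death as the closing one. Death therefore presumably ends some CRRT courses, but the share cannot be computed from the protocol.

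**The case against.** The strongest reply is that these variables are only to be presented. Section 11.3.3.2 names no test for them, and the protocol nowhere says that a shorter stay is better. ICU, hospital and 28-day mortality and the survival curve appear beside them. The artefact is also modest: in the example a 10-point mortality difference moves the mean by 1.2 days. With 31 per group and an assumed standard deviation of 10 days, the standard error of a difference in means is 10 × √(2/31) = 2.5 days (1.8 for 7 days, 3.6 for 14).

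Much of this stands. The effect may be lost in noise, and a careful reader has mortality at hand. But the synopsis and section 3.1.2 plan the durations as between-group comparisons, and mortality figures beside a pooled mean do not show how much of a difference is death and how much is recovery. The per-protocol set in 11.3.1 does not help either, because it does not say whether patients who die count as having concluded the study.

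Three stronger readings are tempting, and the documents do not support them:

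- *All three durations are written to end at death.* Only ICU and hospital stay are. For CRRT duration this is an inference. The synopsis remark that CRRT may stop for various reasons concerns how long the drug is given.
- *Half of the CRRT durations are cut short by death.* The 50% is ICU mortality. Patients can come off CRRT and die later.
- *Higher mortality would make the drug look better.* That needs non-survivors to stay less time than survivors. The protocol does not say so, and the shift is zero or reversed otherwise.

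A preference for medians over means is a matter of presentation and is not part of this point.

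**Conclusion.** The point holds for ICU stay and hospital stay. The end events in 11.2.2 (4)-(5) and the pooled summary in 11.3.3.2 (4)-(5) are fixed by the protocol itself, and following them as written gives two efficacy comparisons without an interpretable direction.

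Under the assumed stays with deaths before survivors' exit (S = 10 to 20, D = 3 to 7), 65% against 50% mortality shortens the mean by 0.45 to 2.55 days. Deaths four days earlier at 50% mortality shorten it by 2.0 days. The first result is conditional on D being below S. The second assumes only equal mortality and unchanged survivor stays. All sizes rest on assumed lengths of stay.

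For CRRT duration the supported statement is narrower: the end event is unwritten, and the same problem is probable but of unknown extent. Overall this is a worthwhile, inexpensive correction to secondary endpoints.

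**What to change.** In 11.3.3.2 (3)-(5), with matching definitions in 11.2.2:

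1. Compare the groups on days alive and off CRRT, days alive and out of ICU, and days alive and out of hospital, each counted to day 28 after CRRT initiation. Score death by day 28 as 0.
2. State whether counting uses the first or the final exit. Days after the chosen exit then need no further record of CRRT restarts or readmissions.
3. Show mortality next to each of these measures.
4. Keep the raw durations as description only, separately for survivors and non-survivors.
5. State when CRRT duration ends, and that it is handled in the same way when death ends CRRT.

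The cost is wording and one counting rule. Stop and exit dates and 28-day vital status are already needed for planned endpoints (sections 8.2.15, 8.3.4 and 11.2.2), and no extra visit is required. The downside is that event-free days are a composite driven partly by mortality, and a survivor still in ICU on day 28 scores 0 as a death does, which is why mortality must be shown beside them.

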### 11.3 Analysis method

#### 11.3.1 General principal of result analysis

The data retrieved from the patients during the study is analyzed by Safety analysis, ITT (Intent-To-Treat) analysis and PP (Per Protocol) analysis.

The Safety analysis is analysis including all data from patients in futhan group who have taken the medication at least once and no-anticoagulation group

The ITT analysis is analysis including all data from patients who have been confirmed whether he or she is dead or alive in futhan group who have taken the medication at least once and no-anticoagulation group. And when there is a missing value or patient drop out before the study is over, the latest value can be analyzed as data acquired at relevant time (Last Observation Carried Forward Method).

The PP analysis is analysis including the data from patients who have successfully concluded the study protocol.

The data regarding validity is principally analyzed by PP analysis, and additionally analyzed by ITT analysis.

The data regarding safety is principally analyzed by Safety analysis.

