#### 7.4.2 Medication that are prohibited to use in combination

The medications listed as following are not allowed to use in combination with nafamostat mesilate.

- ① Medication in similar effect: warfarin, urokinase, FOY, aprotinine, dextrin, prostaglandine etc.

② Anticoagulation medication: heparin, citrate, hirudine etc.

When the patient is needed to use medication that are prohibited to use in combination with nafamostat mesilate under researcher's approval, the patient is excluded from the study immediately and an accurate and detailed documentation should be noted at the last page of the clinical report.

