## 10.2 Disposal of violation on protocol and non-compliance

The principal investigator and researchers should fully recognize and perform the study protocol, hence the protocol is not violated. However, the inevitable violation will be dealt with as follows.

In case of severe protocol violation, researcher should disregard the patient's data from the analysis and the criteria are as follows.

- ① Failure to acquire written consent
- ② Violation of inclusion/exclusion criteria
- ③ Administration of the medication that is prohibited to use in combination during the study.

Other violation of protocol that is decided to be minor and is not thought to influence the study analysis is thoroughly documented with the degree of violation, reason. Afterwards, the violation is evaluated by researcher, funder, monitor, statistician whether the violation has tempered with the study and included in the PP analysis.

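### The set that protocol 11.3.1 calls ITT drops randomised patients by dosing (nafamostat arm only) and by known vital status, so no all-randomised analysis of ICU mortality is defined

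*Protocol*

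**What the plan says.** Section 11.3.1 of the protocol defines three analysis sets. The ITT set takes "patients who have been confirmed whether he or she is dead or alive in futhan group who have taken the medication at least once", and then adds the control arm without any treatment condition: "who have taken the medication at least once and no-anticoagulation group. And when there is a missing value or patient drop out". In the sentence that follows, for missing values and drop-outs, "the latest value can be analyzed as data acquired at relevant time (Last Observation Carried Forward Method". No endpoint is named and none is exempted.

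On the roles of the sets, the section says: "The data regarding validity is principally analyzed by PP analysis, and additionally analyzed by ITT analysis". The primary variable in 11.1.1 is "Mortality at ICU".

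Three other places bear on who is analysed:

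- Section 10.2: "In case of severe protocol violation, researcher should disregard" the patient's data from the analysis. The listed grounds are missing consent, breach of the eligibility criteria, and use of a prohibited drug.
- Section 7.4.2: when a prohibited drug becomes necessary, "the patient is excluded from the study immediately". The list of drugs is introduced as those that may not be given together with nafamostat.
- Section 11.3.3.2 (6): 28-day survival uses "Kaplan-Meier analysis with data of all subjects in the clinical study including censored data".

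**The concern.** An intention-to-treat comparison keeps every randomised patient in the arm assigned, because only that group is protected by the randomisation. The set in 11.3.1 carries the label but not the property. Eligible patients are randomised first and treated afterwards (8.2.10; 8.3.2, items 3 and 4), and they are haemodynamically unstable (6.1). A death or change of plan between randomisation and first dose is therefore possible. It removes a nafamostat patient, while a comparable control patient stays in. Requiring confirmed vital status makes having the outcome a condition of entry for an analysis of that outcome.

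The per-protocol analysis is already the principal one for efficacy, so the ITT analysis is the only safeguard against selection after randomisation. If it is selective too, the trial has no planned estimate of the effect of assignment on its primary endpoint. Making ITT the principal analysis would not help while this definition stands.

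**Working it through.** **The text, rule by rule**

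1. *Dosing.* The at-least-one-dose condition qualifies the nafamostat arm. Control patients receive no study drug, so no counterpart exists. The exclusion is one-sided by construction. The Safety set in 11.3.1 carries the same dosing condition, so the ITT set is in effect the Safety set narrowed further by vital status.
2. *Vital status.* The condition stands in the clause on the nafamostat arm. The grammar leaves open whether it also covers control, and the section does not say at what time status must be confirmed.
3. *LOCF.* If it is applied to mortality, the last value of a patient who leaves the study can only be alive. For a patient of unknown final status, 11.3.1 therefore offers two treatments, exclusion (rule 2) or carrying forward as alive, and does not say which governs. They cannot both act on the same patient at the same time point.
4. *Violators.* 10.2 removes data from the analysis without naming the per-protocol set. 7.4.2 describes the prohibited drugs by reference to nafamostat, which leaves unclear whether control patients given the same drugs are excluded.

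**Inputs for the illustration**

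- From the protocol: 33 per arm (6.3.1, 7.5), anticipated mortality 50%, tolerance 0.15, alpha 0.1 and wastage 5% (6.3.2).
- Assumed, not in the documents: 50% true ICU mortality in both arms; two affected patients, all in the nafamostat arm (2/33 = 6%, close to the planned 5% wastage); true mortality q among drop-outs whose later deaths go unrecorded.

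**The plan's own figure.** 1.645² × 0.5 × 0.5 / 0.15² = 30.06, rounded up to 31; 31/0.95 = 32.6, rounded up to 33. Both stated figures are reproduced, and nothing here disputes them.

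**Dosing condition.** Expected deaths in 33 patients: 33 × 0.5 = 16.5.

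- Both undosed patients die: (16.5 − 2)/(33 − 2) = 14.5/31 = 46.8%, which is 3.2 points too low.
- Both undosed patients survive: 16.5/31 = 53.2%, which is 3.2 points too high.

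**Two patients of unknown final status**

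| q | Carried forward as alive: (16.5 − 2q)/33 | Excluded: (16.5 − 2q)/31 |
|---|---|---|
| 0.5 | 15.5/33 = 47.0% | 15.5/31 = 50.0% |
| 0.8 | 14.9/33 = 45.2% | 14.9/31 = 48.1% |
| 1.0 | 14.5/33 = 43.9% | 14.5/31 = 46.8% |

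Carrying forward lowers recorded mortality by 3.0 to 6.1 points, and excluding lowers it by 0 to 3.2 points. The two readings of 11.3.1 thus give different answers from the same data. If both arms lose the same number with the same q, both fall equally and the difference between arms is unchanged.

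**The case against.** Several defences have force.

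- *LOCF.* A reader might infer that the plan counts drop-outs as alive. The text does not go that far. The rule is permissive and tied to no endpoint, a drop-out later confirmed dead counts as dead, and one of unknown status may be excluded instead. What stands is that LOCF is unsuitable for mortality if used, and that the text does not rule it out.
- *Kaplan-Meier.* A reader might see a contradiction between LOCF and the censoring in 11.3.3.2 (6). The two can coexist: censoring is the specific rule for one secondary endpoint, and LOCF is a general option.
- *Prohibited drugs.* A reader might infer that only nafamostat patients are removed. The 10.2 item on prohibited drugs names no arm, and neither does the related drop-out ground in 10.1 (item 8). One-sidedness is only one reading of 7.4.2. The next paragraph of 10.2 mentions the per-protocol analysis, so the section may have been meant for that set alone. This is an ambiguity to resolve, not a demonstrated asymmetry.
- *Frequency.* The circuit priming fluid already contains nafamostat (7.2.2), so the undosed interval is probably short. ICU deaths occur in hospital, so unknown status should be uncommon. For scale, the 90% half-width of the difference at 33 per arm and 50% mortality is 1.645 × √(0.5/33), about 20 points, well above the shifts illustrated.

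None of this restores the randomised comparison. Nor is it a detail left to a later analysis plan, because the protocol states the definition outright.

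**Conclusion.** Wrong as written. The set labelled ITT removes undosed patients from the nafamostat arm only, and it admits patients on condition that their vital status is known. With the per-protocol analysis principal, no analysis of ICU mortality in all randomised patients is defined. The unrestricted LOCF option and the open-ended exclusions in 10.2 and 7.4.2 add uncertainty about who is counted and how.

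A reader might infer that these rules mostly favour nafamostat. The documents do not support that. An undosed patient may have died or may have improved, the effect of the vital-status condition depends on who is lost, and LOCF shifts the difference between arms only if loss, or mortality among those lost, differs between them.

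The size is unknown. About 3 points of mortality for two affected patients (46.8% or 47.0% against 50%) rests on assumed one-sided events and is illustrative only. The sample size of 31 and 33 per arm is unaffected.

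**What to change.** - **11.3.1:** define ITT as every randomised patient, analysed in the arm assigned, with no condition on dosing, vital status or prohibited drugs. Patients without valid consent are the only exception.
- **11.3.1:** state that LOCF does not apply to mortality or survival. Use the vital status already collected at discharge and at 28 days after CRRT initiation (8.2.15, 8.3.4). Where status stays unknown, censor at last contact in the Kaplan-Meier analysis and show best-case and worst-case results for the binary endpoint.
- **10.2 and 7.4.2:** limit the removal of eligibility violators and users of prohibited drugs to the per-protocol set, and say that the same rule holds in both arms. Which drugs are permitted is not at issue.

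The cost is rewording three sections and a little more analysis. The necessary vital-status follow-up is already planned.
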